### Interim analyses

Interim analyses will be carried out using the statistical methods described above immediately after JOBS Program Germany have been completed (Fig. 1, *t*_*1*_). The research team of Kassel University is obliged to provide research reports to the funder on a yearly basis. Thus, interim results will be reported to the funder. We will also report interim results to the BZgA. The trial will not be modified or terminated before the scheduled 6 months regardless of the results of any interim analyses.

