### Statistical methods

Statistical methods will include t-tests (or equivalent tests for proportions) as well as linear and (binary) logistic regression models. We will compare primary and secondary outcomes between the intervention and waiting control groups.

Reintegration into the labor market (employed vs. unemployed) and the type of contract (temporary vs. permanent) will be assessed using t-tests (or equivalent test of proportions) and logistic regression models. In all analyses, we will treat Likert-Type items as continuous variables. For life-satisfaction, depressive symptoms, and psychological distress, we will first construct (additive) indices. We will then test mean differences in the respective indices between intervention and waiting control groups using t-tests. In multivariate analyses, we will use linear regression models to adjust for baseline-measures of the respective outcomes. Additional models will also adjust for socio-demographic characteristics and indicators of labor market biography, such as the duration of unemployment. We proceed in a similar fashion to analyze self-esteem, self-efficacy and our secondary outcomes job satisfaction and job-search intensity.

To test for potential effect modifications, we include interaction terms between our treatment-indicator and the respective moderators (job-search intensity, duration of unemployment) in the respective regression models.

All multivariate analyses will include controls for socio-demographic variables and (un-)employment history. We will repeat our main analyses stratified by gender. All analyses will be carried out according to the  “intention-to-treat” principle. Participants will be treated as belonging to the group to which they were originally (randomly) allocated. We tolerate low proportions of missing values of up to 5%, and perform listwise-deletion (complete-case analyses). If the proportion of missing values exceeds the predefined threshold of 5%, we will treat missing values by means of multiple imputation [31–33].

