### Frequency and plans for auditing trial conduct

The research team at the University of Kassel will hold meetings with BZgA, National Association of Statutory Health Insurance Funds, and SOKO on a monthly basis or more frequently if required (e.g., during the time of recruitment). In these meetings, any organisational aspects, including but not limited to recruitment of locations and participants, participation rates in JOBS Program Germany, and overall time schedule are monitored and discussed. Corrective actions to preserve the integrity of the study will be taken if deemed appropriate.

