## Dissemination plans

Results will be published via multiple channels. The funding agency, the Federal Ministry of Education and Research, will be informed on a regular basis, at least once a year, about the progress of the project and also about the interim and final results.

Furthermore, the cooperating partners, above all the BZgA, will be informed about the study results by the research team at the University of Kassel. The BZgA covers a wide range of media, including regular newsletters, which can provide information about the JOBS Program Germany and the respective study results.

The research team at the University of Kassel will report all results of the confirmatory evaluation study independently from the founding party or any cooperating partners, and regardless of strength and direction (positive, negative, null-results) of the effects. This reporting will take place in the context of university teaching, at national and international labor- and public health-related conferences, and in the form of publications in international peer-reviewed journals. Authorship eligibility will be based on the recommendations of the international committee for medical journals editors (ICMJE).

The various publication channels ensure that no result remains unknown and that the dissemination will be tailored to the different target groups. In addition to the publication of the results in the international scientific community, it is ensured that university students, the unemployed in Germany, health organizations and health insurance companies, institutions of employment promotion and their practitioners, as well as political decision-makers will be fully informed about the study results. This ensures low-threshold and transparent accessibility of the results and prevents publication bias.

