### Plans for communicating important protocol amendments to relevant parties

Substantive modifications to the study protocol, including but not limited to changes of the study objectives, the eligibility criteria, the sample sizes, the allocation, the outcomes, or the statistical analyses will be discussed with all cooperation partners. Any such changes will be documented and published as amendments to this study protocol. Amendments shall also be made to the trial registry entry in the DRKS. Specific attention must be drawn to the course of the SARS-CoV-2/COVID-19 pandemic that might impair participant recruitment or may hamper the education of potential trainers.

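### Between-arm post-test results go to the BZgA, which is close to the field work, with no stated limit on their use before the 6-month interviews are complete

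*Protocol article*

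**What the plan says.** All of this is in the protocol article.

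- **Interim analyses.** "Interim analyses will be carried out using the statistical methods described above immediately after JOBS Program Germany have been completed". The methods referred to are those of the Statistical methods section, which states: "We will compare primary and secondary outcomes between the intervention and waiting control groups". The interim results are therefore by arm.
- **Recipients.** The research team is "obliged to provide research reports to the funder on a yearly basis", and the section continues: "Thus, interim results will be reported to the funder". It then adds: "We will also report interim results to the BZgA".
- **Safeguard.** The same section says that the trial will be neither changed nor ended early, whatever the interim results show.
- **Position of the BZgA.** Under Study setting, it coordinates the programme across about 230 locations, and SOKO gathers the data for it. Under the section on auditing trial conduct, the research team meets the BZgA and SOKO monthly or more often. Under Dissemination plans, the BZgA's media are described as "including regular newsletters, which can provide information about the JOBS Program Germany and the respective study results".
- **Design.** Trial design describes the trial as non-blinded. Outcomes says that all outcomes come from telephone interviews.

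**The concern.** The between-arm effect at t1 is passed to the organisation closest to delivery and interviewing, at a time when t2 may be largely uncollected. Nothing in the sections on interim analyses, auditing or dissemination says that the BZgA must hold it in confidence until t2 is done.

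If word of a favourable or unfavourable t1 result reaches locations, trainers, interviewers or participants, it can colour how people answer at t2. It can also change who answers. Table 1 expects 1200 respondents at t1 and 900 at t2, so 300 are lost in that interval and there is room for response to differ by arm. The t2 comparison is the one the sample size is built on. No decision depends on the interim result, so the trial gains nothing from early release.

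**Working it through.** **1. Which time point carries the trial.** Inputs from Sample size: d = 0.2, 85% power, two-sided alpha 0.05.

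n per group = 2 × (1.960 + 1.036)² / 0.2² = 2 × 8.98 / 0.04 ≈ 449. The plan says 450, so its figure is reproduced; power at 450 per group is 0.851.

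Table 1 places these 450 at t2: 1500 × 0.80 × 0.75 = 900 in total.

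**2. How much of t2 is outstanding at release.** Inputs from Procedure: about 60 courses from April to September 2021, t1 within 4 weeks of the course, t2 at 6 months.

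Assumptions: courses evenly spread from 1 April to 30 September; t2 due 183 days after each course; an equal share of t2 interviews per course, 900 / 60 = 15.

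- t1 closes on 30 September + 28 days = 28 October 2021.
- By then t2 is due only for courses that ended by about 28 April. At 60 / 6 = 10 courses a month, that is about 10 of 60, or 17%.
- Outstanding: 50 / 60 = 83%, and 50 × 15 = 750 of 900 interviews.

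The result depends on the release date:

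| Release after last course | t2 outstanding of 900 | Share |
|---|---|---|
| 28 days (t1 closes) | 750 | 83% |
| 60 days | 600 | 67% |
| 90 days | 450 | 50% |
| 120 days | 315 | 35% |
| 150 days | 165 | 18% |
| 183 days | 0 | 0% |

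**3. Sensitivity to the course calendar.** With courses from 15 April to 30 September, 825 of 900 (92%) are outstanding when t1 closes. With 1 April to 31 August, or 1 May to 30 September, all 900 are. The August calendar puts the last t2 at 2 March 2022, closest to the trial end of February 2022 given in Procedure. Across the calendars tried, the outstanding share is 83% to 100% when t1 closes, 50% to 60% at 90 days and 35% to 42% at 120 days. If results were analysed and released course by course, no t2 interview of that course would yet be due.

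**4. What the safeguard covers.**

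- Stopping early or changing the trial because of t1: ruled out.
- Alpha for the t2 test: unaffected, because t1 is a planned assessment and not an early look at t2 data.
- Who may know the t1 effect while t2 is collected: not addressed.

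**The case against.** The strongest case on the other side has these parts.

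- **The no-modification rule is explicit.** This stands. There is no stopping or alpha problem.
- **A reader might infer that other sections reopen modification.** The auditing section says "Corrective actions to preserve the integrity of the study will be taken if deemed appropriate", and the amendments section says substantive changes "will be discussed with all cooperation partners". The article does not support that inference. The meetings concern organisational matters such as recruitment and schedule. The amendment section is a general plan with documentation, publication and registry entry, and it singles out the pandemic. Neither permits changes driven by interim results.
- **The onward chain is inferred.** Only two recipients are named. The newsletter sentence speaks of study results in general and does not say that interim results will be circulated. This stands as a limit on how likely a leak is. It does not supply a restriction.
- **The funder has no stated contact with participants.** This stands, so the point rests on the BZgA.
- **No report date is given, and funder reports are yearly.** This stands. The word about immediacy governs the analysis, not the report.
- **Participants already know their arm.** This stands. Only the added effect of hearing a t1 result counts, and the article gives no basis for its size. Employment, contract type and hours are self-reported but factual, and probably less open to influence than the symptom scales.
- **This is a condensed article.** A full protocol exists and may hold confidentiality terms. That would be an answer if it does. But the release to the BZgA is stated here as a rule; it is not a detail left out.

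**Conclusion.** The point holds as a risk of avoidable bias. The plan releases by-arm t1 results to a body that coordinates the locations, for which the interviews are conducted and which has public channels, and it sets no limit before t2 is complete. The rule against modification does not reach this.

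The exposure, on an even spread of courses, is about 83% of t2 interviews if release comes when t1 closes and about 50% if it comes 3 months after the last course. That most of t2 is outstanding at release is therefore conditional on an early report, and the article does not fix the date.

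A reader might wish to translate this into an inflated false-positive rate at t2. The documents do not allow it, because any assumed shift in reporting would be arbitrary. This is a cheap improvement, not a fault that invalidates the design.

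**What to change.** Amend the Interim analyses section, and Dissemination plans to match:

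- By-arm t1 results stay with the university analysts. They are not given to the BZgA, SOKO or other operating partners until the last t2 interview is complete.
- Until then those partners receive only figures pooled over both arms on recruitment, participation and retention.
- The yearly funder report uses the pooled figures. If the funding terms, which are not shown, require by-arm results, these are given in confidence with no onward release before t2 is complete.

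If the full protocol already contains such terms, the article need only say so.

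Cost: short edits to two sections, with no change to sample size or alpha. On the April to September calendar, release to partners moves from about the end of October 2021 to about 1 April 2022, roughly 5 months later. The analysts would still know the t1 effect, so the change protects the field side and not the analysis side.

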### Frequency and plans for auditing trial conduct

The research team at the University of Kassel will hold meetings with BZgA, National Association of Statutory Health Insurance Funds, and SOKO on a monthly basis or more frequently if required (e.g., during the time of recruitment). In these meetings, any organisational aspects, including but not limited to recruitment of locations and participants, participation rates in JOBS Program Germany, and overall time schedule are monitored and discussed. Corrective actions to preserve the integrity of the study will be taken if deemed appropriate.

## Dissemination plans

Results will be published via multiple channels. The funding agency, the Federal Ministry of Education and Research, will be informed on a regular basis, at least once a year, about the progress of the project and also about the interim and final results.

Furthermore, the cooperating partners, above all the BZgA, will be informed about the study results by the research team at the University of Kassel. The BZgA covers a wide range of media, including regular newsletters, which can provide information about the JOBS Program Germany and the respective study results.

The research team at the University of Kassel will report all results of the confirmatory evaluation study independently from the founding party or any cooperating partners, and regardless of strength and direction (positive, negative, null-results) of the effects. This reporting will take place in the context of university teaching, at national and international labor- and public health-related conferences, and in the form of publications in international peer-reviewed journals. Authorship eligibility will be based on the recommendations of the international committee for medical journals editors (ICMJE).

The various publication channels ensure that no result remains unknown and that the dissemination will be tailored to the different target groups. In addition to the publication of the results in the international scientific community, it is ensured that university students, the unemployed in Germany, health organizations and health insurance companies, institutions of employment promotion and their practitioners, as well as political decision-makers will be fully informed about the study results. This ensures low-threshold and transparent accessibility of the results and prevents publication bias.

### Plans to give access to the full protocol, participant level-data and statistical code

Access to the full study protocol is regularly granted to the funder and, upon request and after a formal agreement on confidentiality, to interested scientists. Because informed consent, sought from the participants, does not include general release of the data, we will not publish the participant level datasets. Statistical code will be made available via appropriate data repositories.

### Plans for communicating important protocol amendments to relevant parties

Substantive modifications to the study protocol, including but not limited to changes of the study objectives, the eligibility criteria, the sample sizes, the allocation, the outcomes, or the statistical analyses will be discussed with all cooperation partners. Any such changes will be documented and published as amendments to this study protocol. Amendments shall also be made to the trial registry entry in the DRKS. Specific attention must be drawn to the course of the SARS-CoV-2/COVID-19 pandemic that might impair participant recruitment or may hamper the education of potential trainers.

## Discussion

Compared to the employed, the risk of morbidity is significantly higher for unemployed persons in Germany. Furthermore, the prevention and health promotion hardly reach the unemployed. The JOBS Program is a health promotion program that specifically targets the unemployed. It combines job application training with elements of social learning theory and self-efficacy to improve the reintegration into the labor market and (mental) health.

In this confirmatory study, we assess whether the positive effects of the JOBS Program in the United States [7], Finland [11] and the Netherlands [17] can be replicated in the German context. The greatest strength of our study design is that we implement a randomized controlled trial in a large-scale, countrywide field experiment, thus, maximizing both the internal and external validity of our results. However, even this “real-life” setting has certain limitations. Most importantly, our trial will be conducted during the current SARS-CoV-2/COVID-19 pandemic that will probably affect, directly or indirectly, most of our outcomes, such as reintegration into the labor market and mental health. Assuming that the pandemic will have comparable effects for both the intervention group and the waiting control group, we do not expect large impacts on the internal validity of our results. However, our time schedule might be delayed by future government measures (“shutdown”) that temporarily hamper implementation of JOBS Program Germany.

Despite the discussed limitations, our study potentially provides the basis for a valuable addition to the German employment promotion and social security system. If the positive effects on reemployment and (mental) health can be replicated in the German context, the JOBS Program Germany could be implemented on a regular, long-term basis to benefit the unemployed. Since the administrative infrastructure is already in place and the relevant agencies are already involved, implementation of the JOBS Program Germany could perspectively be extended.

## Trial status

This is version 1 of the study protocol, submitted in December, 2020. Recruitment is expected to start in March, 2021. Recruitment will approximately be completed by the end of September 2021.

## Data Availability

Not applicable.

## Abbreviations

BZgA: Federal Centre of Health Education (Bundeszentrale für gesundheitliche Aufklärung)
CATI: Computer-assisted telephone interview
DASS-21: Depression-Anxiety-Stress-Scale
PHQ-9: Patient-Health Questionnaire 9
SWLS: Satisfaction with life scale
WHO-5: World Health Organization well-being index
